### Data collection plan

The study will be conducted at a single center, which will serve as the coordinating hub and be responsible for all stages of the RCT.

Verification and authenticity of the data quality entered into the electronic clinical record and printed documents will be carried out by the research team at our Clinical Research Unit (UPECLIN) according to the monitoring plan, during the execution and at the end of the clinical study.

To prevent data loss, we will develop standardized data collection forms and monitor the collected data regularly. Patients will be contacted frequently by telephone or social media, with updates often provided during these contacts. The appropriate clinical support will be offered to patients to minimize losses. Disease progression resulting in death or amputations will be defined as endpoints and will not be classified as data loss.

### Source documents

Source documents are original records that contain essential information for the reconstruction and evaluation of the clinical trial. They will be used to verify the accuracy and completeness of the data collected. The following principles will apply:

Complete Records: All relevant data related to the study will be recorded completely and accurately in the source documents. This includes, but is not limited to, medical records, laboratory test results, scales, questionnaires, and ICF.Access and Storage: Source documents will be stored in a secure location with passcode-restricted access.Confidentiality: The confidentiality of participant data will be satisfied in all source documents. Identifiable information will be protected by data protection guidelines.Verification and Auditing: Source documents will be available for verification and inspection by ethical regulatory authorities if necessary.

### Data standards

Data collected from participants will be entered into the electronic case report form system (e-CRF) accurately and by the records in the source document. The study will be monitored regularly by qualified clinical monitors to verify adherence to the most current approved protocol, the accuracy of recorded data, the rights and safety of participants, and whether the study is being conducted by applicable regulatory requirements. Monitoring reports will be generated and reviewed periodically. Furthermore, inspections may be conducted by regulatory authorities or ethics committees to ensure compliance with legal and ethical requirements.

### Data protection

The privacy and confidentiality of participant data will be strictly protected throughout the study. Measures include:

Confidentiality: All data collected will be treated as confidential. Only authorized members of the research team will have access to identifiable participant data.Anonymization: Participant data will be anonymized whenever possible, replacing identifiable information with unique codes. This will ensure that data cannot be directly linked to participants.Secure storage: Data will be stored in secure systems, protected by passwords and other cybersecurity measures. Physical access to data will be restricted to secure areas in the research center.Data Sharing: Any sharing of data with third parties will be carried out anonymously, with restricted purposes of scientific research and data analysis. Requests should be made directly to the main researcher, by email.Compliance with Regulations: The study will comply with all applicable data protection laws and regulations, including the Brazilian General Data Protection Law (LGPD).

### Blinding

Results will be anonymized, tabulated, and sent to evaluators and statisticians in a blind manner. They will be external members, not belonging to the study execution team, and will electronically receive the images of the ulcers identified only by the participant’s number and an electronic form with the variables already described for ulcer assessment.

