**Methods:**

An open randomized clinical trial will be carried out with two groups of twenty patients with CLI: In group 1, 2g of abdominal adipose tissue will be taken to produce ASCs. These cells will then be expanded in a lab (cell processing center) for 14–21 days before being applied to the lesion using bio-dressings and perilesional subcutaneous injections. Group 2 will receive conventional treatment with hydrogel-based dressing. There will be regular clinical assessments, supplementary tests, and photo documentation. The main efficacy outcome will be partial or complete healing of the wound. Safety outcomes will be monitored for infections, gangrene, amputations, and death. Participants will be monitored for 90 days. Cases of major amputation of the studied limb will not be included. The results will be evaluated by an independent external evaluator who is blind to the groups. Considering the high prevalence and socioeconomic consequences related to CLI and limb amputation, this study is expected to provide a positive social and financial impact on the Brazilian Unified Health System.

ClinicalTrials.gov: NCT06326203.

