## Method

### Study design

This is a phase I/II, single-center, randomized clinical trial (RCT), PROBE (Prospective Randomized Open, Blinded Endpoint), controlled to evaluate the safety and efficacy of using ASCs to treat injuries in patients with PAD and advanced-stage CLI. The study was designed to attend the guidance Standard Protocol Items: Recommendations for Interventional Trials for clinical trial protocols (SPIRIT). (S1 File SPIRIT checklist)

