#### Group 1.

Cell Therapy Treatment Group: Participants will receive expanded ASC treatment. The participant will undergo a surgical debridement procedure of the ulcer so that it is in its best condition (Visit 1). Subsequently, the participant will receive an ASC application via perilesional subcutaneous injections and a bio-dressing produced by the study team, also containing ASCs (the dressing containing ASC will remain in contact with the ulcer for 7 days in a single session). After removing the biological dressing, the participant will receive local care for the ulcer with a topical hydrogel dressing, dry gauze, and a crepe bandage, changed at least once a day.

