### Intervention

In the treatment group, the active component of this project’s cell therapy product is autologous ASCs [31–33], which will be expanded in the Laboratory (Cell Processing Center). The ASC will be made available to the patient in two presentations for use in a single treatment session: injectable solution and stable bio-dressing. The dosage planned for this clinical trial will be a single application of the products.

The procedure for applying the advanced cell therapy product proposed in this clinical trial will be carried out after locoregional (preferred) or general anesthesia, at the discretion of the anesthesiologist who will accompany the procedure, considering the participant’s clinical conditions, since the procedure cannot be performed without adequate analgesia. The application of injections and dressings will follow the rules of surgical procedures, carrying out antisepsis, placement of sterile drapes, manipulation of surgical materials, and opening of envelopes containing the products to be applied in a sterile manner.

Initial surgical cleaning and debridement will be carried out on the wound to make it ready to receive the treatment. Subcutaneous applications of 0.1 mL of the product consisting of the plasma solution and expanded autologous ASC will then be carried out every 1 cm from the edge of the ulcer (in the subcutaneous layer of the intact skin at the perimeter of the lesion), so that approximately 1x10^4^ ASCs are injected by puncture.

After the injections, the topical application of the stable bio-dressing will be carried out containing the ASCs on a membrane FIBRACOL™ Plus (Systagenix Brazil, dressing containing 90% collagen and 10% calcium alginate) with the same plasma solution containing cells in the proportion of 1x10^4^ ASCs per cm^2^ of the ulcer area to be covered (Fig 2). The dressing will be covered with rayon gauze (identifying the end of the primary dressing), the secondary dressing will be composed of a thin layer of moistened gauze with 0.9% saline, a layer with dry gauze, and, finally, a crepe bandage. Only the secondary dressing will be changed daily by the participant or their caregivers, according to instructions given by the study team. After 7 days, the ASCs absorption phase will be completed and the participant will return for reassessment of the ulcer, moving on to the phase in which the dressing will contain only hydrogel.

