Follow-up of patients will continue for 120 days from the moment they receive treatment with the proposed advanced cell therapy. Time required for screening and preparations will not count toward the study follow-up period. Participants will be reassessed on days 7, 30, 60, 90, and 120 days after randomization. The closing assessment will be carried out after 120 days (assessment 6). After completing their participation in the study, the participants will be referred for routine follow-up at the vascular surgery outpatient clinic of the Clinical Hospital of the Faculty of Medicine of Botucatu. During this period, extra visits may occur, if necessary (S3 File Table 1 Assessment Schedule).

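### Labelling ulcer images with the participant's number lets the blinded reader link them, so an image from bio-dressing removal, if sent, could reveal the arm when the endpoint image is read

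*Protocol article*

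**What the plan says.** Study design describes the trial as "PROBE (Prospective Randomized Open, Blinded Endpoint", and the abstract's Methods add: "The results will be evaluated by an independent external evaluator who is blind to the groups". The Blinding section gives the mechanism: "Results will be anonymized, tabulated, and sent to evaluators and statisticians in a blind manner". These people are external to the study team and "will electronically receive the images of the ulcers identified only by the participant’s number", together with an electronic form for the ulcer variables.

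The two arms are handled differently around the time of treatment. In Group 1, injections "will then be carried out every 1 cm from the edge of the ulcer" (Intervention), and "the dressing containing ASC will remain in contact with the ulcer for 7 days in a single session" (Group 1). The Intervention section then has the participant return after 7 days for the ulcer to be reassessed, before moving to hydrogel. The control group has hydrogel, gauze and bandage from the start, changed at least daily, with no injections and no membrane. Both arms have surgical debridement at Visit 1.

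On photographs, the abstract says only: "There will be regular clinical assessments, supplementary tests, and photo documentation". The Participant timeline lists the visits: "Participants will be reassessed on days 7, 30, 60, 90, and 120 days after randomization". Total epithelialization is part of the primary efficacy outcome. Partial healing, a secondary outcome, is assessed by measuring ulcer area in ImageJ.

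**The concern.** In an open trial with blinded endpoint reading, the external image reading is the main protection for an outcome that involves visual judgement, and total epithelialization is such an outcome. The protection depends on the reader not knowing the arm when reading the endpoint image.

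A label made of the participant's number hides the name but keeps the images of one person together. That is harmless if no image shows the treatment. Here one arm has a ring of punctures and a membrane on the wound bed, and the ulcer is examined as that phase ends. A photograph from that examination is the one most likely to give the arm away. The shared number would then carry that knowledge to the same participant's other images. Knowledge of the arm could tip borderline calls, most plausibly towards the arm that the reader expects to do better.

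**Working it through.** **1. What the label allows.** The Blinding section names one identifier, the participant's number, and says that it is the only one. No code at image level is described, so two images of the same participant can be matched. This follows from the stated rule.

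**2. Whether the arms can look different.**

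| Feature | Group 1 | Group 2 |
|---|---|---|
| Surgical debridement at Visit 1 | yes | yes |
| Perilesional injections, 1 cm apart | yes | no |
| Collagen/alginate membrane for 7 days | yes | no |
| Hydrogel, gauze, bandage | after membrane removal | from the start |

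The number of injections follows from the eligible ulcer size (1 to 20 cm², Inclusion criteria). For a circular ulcer the perimeter is 2 × √(π × area):
- 1 cm²: 2 × √3.14 = 3.5 cm, about 4 punctures.
- 20 cm²: 2 × √62.8 = 15.9 cm, about 16 punctures.

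This counts injections given. How many leave a visible mark a week later is not stated.

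**3. Whether a revealing image reaches the reader.** The article does not say. Three points make it plausible: photography is described as regular, the Blinding section excludes no visit, and following ulcer area needs serial images. The examination that matters is the one that ends the bio-dressing phase (Intervention). The timeline's day 7 is counted from randomization. Allocation is opened at adipose collection and expansion takes 14 to 21 days, so a literal day 7 would come before the application in Group 1. The point therefore does not rest on that visit label.

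**4. Which image is the endpoint image.** No time point for total epithelialization is named. The abstract gives 90 days of monitoring, and the timeline gives 120 days. The endpoint image is therefore whichever image the primary reading uses.

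**5. What a biased reading could do.** No figure in the article measures this, so what follows is an illustration.

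The planned size, first, reproduces. With 75% against 30%, two-sided 5%, 80% power and pooled variance, the mean rate is 0.525 and

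n = [1.96 × √(2 × 0.525 × 0.475) + 0.842 × √(0.75 × 0.25 + 0.30 × 0.70)]² / 0.45² = (1.384 + 0.531)² / 0.2025 = 18.1,

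or 19 per group, against the stated 20.

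With 20 per group, one changed reading moves an arm by 1/20 = 5 points. Now assume no true effect, with healing at the article's control rate of 30% in both arms. Let a share q of unhealed Group 1 ulcers be read as healed, with one result per participant. The Group 1 rate as read is 0.30 + 0.70q, and the expected number of misread participants is 20 × 0.70 × q = 14q. Summing exact binomial probabilities over all outcomes with p < 0.05 in either direction gives:

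| q | Expected misread | Group 1 rate as read | Fisher | Pearson chi-square |
|---|---|---|---|---|
| 0 | 0 | 30.0% | 2.5% | 5.3% |
| 5% | 0.7 | 33.5% | 2.9% | 6.0% |
| 10% | 1.4 | 37.0% | 4.1% | 7.9% |
| 20% | 2.8 | 44.0% | 9.1% | 15.0% |
| 30% | 4.2 | 51.0% | 17.8% | 26.4% |

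Occasional misreading does little. Misreading 20% to 30% of unhealed Group 1 ulcers would multiply the Fisher false-positive rate by about 3.7 (9.1/2.5) to 7.1 (17.8/2.5).

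**The case against.** The strongest reply is that harm needs a chain of steps, none of them stated: the dressing-removal image is sent, it shows the arm, it is read before or with the endpoint image, the reader recognises the arm, the ulcer is borderline, and the call is biased. Small punctures may have faded, and once the membrane is off both arms receive the same dressing. Area measurement in ImageJ makes the assessment less purely visual. Reading order and image sets are also details that an article may leave to the full protocol and the assessment schedule, which are supplementary files not shown here. Finally, linked reading has a legitimate use, because partial healing and ulcer enlargement are changes over time and a participant may have up to 3 ulcers.

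Most of this stands, and it limits the point to a risk. What it does not remove is the labelling rule itself, which the article states. The need for change over time can be met by linking codes after the reading.

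Stronger readings are tempting, but the article does not support them:
- A reader might infer that one image necessarily unblinds all later ones. That depends on which images are sent and in what order, and neither is given.
- A reader might infer that the participant's number shows the order of visits. It identifies a person, and the article says that it is the only identifier.
- A reader might infer that all 20 Group 1 participants are exposed. Nothing says how many images would show a treatment sign.
- A reader might infer that the abstract's blinding claim is contradicted because evaluators see only images and the ulcer form. The Blinding section also has tabulated results sent blind, and the article states openly that treatment is open.

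**Conclusion.** The point holds as a risk that should be closed. The stated label allows linkage, Group 1 alone has treatment features that could be visible, and the Blinding section states no safeguard that separates the dressing-removal image from the endpoint image. The affected outcome is the reading of total epithelialization. Limb salvage, the other part of the primary efficacy outcome, does not depend on image reading.

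The size of any bias is unknown. The 5 points per changed reading is arithmetic on 20 per arm. The false-positive rates rest on assumed misreading shares, confined to Group 1, and an assumed 30% healing in both arms. The conclusion also assumes that the dressing-removal image is in the reader's set and that no safeguard stands in the supplementary files. If either assumption fails, a sentence in the Blinding section saying so would settle the matter.

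**What to change.** In the Blinding section, replace the participant's number with a random code for each image. Specify that:
- the endpoint image for total epithelialization is read on its own, in random order across participants;
- the image taken at bio-dressing removal is withheld from the reader until the endpoint reads are locked, which also helps if a reader could recognise an ulcer by its appearance;
- codes are linked in the database after reading, to compute change in ulcer area.

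The cost is a code list and a file-renaming step, which the Clinical Research Unit could run. No extra reader and no change to treatment or visits are needed. The downside is that the reader loses earlier images as context, so each photograph needs a scale and an ulcer identifier.

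Cropping the skin around the ulcer is optional, since it could hinder judgement of the epithelial edge. Noting in the abstract that pain and quality of life are reported by participants who know their arm is also optional. The change must be made before the first images are sent, because a reader who has seen linked images cannot be re-blinded.

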### Sample size and Statistics

The results obtained through the primary and secondary outcomes will be tabulated weekly in an electronic spreadsheet by the study monitoring team. A sample of 40 participants is estimated. The data will initially be evaluated using descriptive statistics, with median/variance and/or mean/standard deviation analyses for quantitative variables and contingency table analyses for categorical/qualitative variables. To effectively recruit the intended number of participants, our strategy involves having study team members to actively engage with patients in the outpatient clinics and wards of HC-FMB. This direct approach will ensure that we connect with a wide range of patients who meet the criteria to participate in the study, maximizing our chances of success.

All data monitored in the study for Group 1 (cell therapy) and Group 2 (control) will be statistically compared. Quantitative data will be evaluated for their distribution (using the Shapiro-Wilk normality test) and compared using the T-test or the Wilcoxon test, depending on the type of distribution of the variables. For categorical variables, differences will be evaluated using Pearson’s Chi-square test or Fisher’s exact test. Bonferroni coefficient and multivariate analysis will also be used. In all statistical tests, the significance level of the independent variable will be set at 5% (p < 0.05).

Finally, the evaluation of the entire data set using multiple correspondence analysis (MCA) is proposed. For its application, each quantitative variable will be categorized according to the distribution quartiles of their respective data.

Categorical variables will be evaluated by means of Fisher’s exact test, continuous variables will be compared with non-parametric methods such as the Mann-Whitney test or U test, pairwise comparisons will be evaluated with the Wilcoxon test, multivariate analyses will be evaluated with regression analysis Cox curves, long-term clinical analyzes will be compiled into Kaplan Meir curves.

To prevent data loss, we will implement the measures previously outlined. However, if a category has missing data for 50% or more of the participants, that category will be removed from the analysis. In some cases, where only a portion of the data is missing, the missing data may not be included in the analysis. If more than 10% of the data is missing, we will consider using seasonal adjustment with linear interpolation, especially if the data shows trends and seasonal patterns. For data sets with a significant amount of missing data (while still less than 50%), multiple imputations will be employed.

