### Inclusion criteria

Ability to understand and accept written free informed consent form (ICF) (S2 File ICF in Portuguese and English).Both sexes, of any ethnic origin.Age between 18 and 90 years old at the time of signing the ICF.Absence of distal pulses of the affected lower limb (anterior tibialis, dorsalis pedis, and posterior tibialis).PAD with CLI, classified as Fontaine IV [27] or Rutherford 5 and 6 [28].Between 1 and 3 ulcers on the foot or distal third of the leg of at least 1 cm^2^ up to a maximum of 20 cm^2^ in area.Previous treatment with conventional dressings, antibiotic therapy, or debridement (if necessary) and no improvement in a minimum period of 3 weeks.Having an ankle-brachial index (ABI) < 0.9 for below-knee arteries (anterior tibial, dorsalis pedis, posterior tibial, and fibular) or ABI > 1.3 in one or more of those arteries in association with type 2 diabetes (disease duration > 5 years) [29,30].Not undergoing revascularization treatment or failed revascularization treatment in the last 12 months.Impossibility of arterial revascularization of the affected limb and/or incomplete revascularization of that limb (subjected to endovascular or surgical treatment that was unable to reestablish blow-knee perfusion), meaning exhaustion of all surgical therapies.Optimized drug treatment for PAD and comorbidities.Availability to attend medical appointments.

After the participant’s inclusion in the study, regardless of the group allocated, they will be sent to collect laboratory tests: blood glucose, glycated hemoglobin, total cholesterol, high-density lipoprotein (HDL), low-density lipoprotein (LDL), triglycerides, complete blood count, uric acid, urea, creatinine, C-reactive protein (CRP), sodium, potassium, and immunomodulatory cytokine profile.

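### Two conflicting unadjusted test rules cover the continuous secondary outcomes, and neither uses the baseline values known at entry

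*Protocol article*

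**What the plan says.** All test rules are in the protocol article, Sample size and Statistics.

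- **First rule.** Quantitative data are checked for their distribution "using the Shapiro-Wilk normality test" and then "compared using the T-test or the Wilcoxon test, depending on the type of distribution of the variables".
- **Second rule.** The section's last paragraph states that "continuous variables will be compared with non-parametric methods such as the Mann-Whitney test or U test". It gives Wilcoxon a separate role: "pairwise comparisons will be evaluated with the Wilcoxon test".
- **Models.** Multivariate analysis is mentioned without covariates. The only model named is for survival data: "multivariate analyses will be evaluated with regression analysis Cox curves".

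On baseline information, Inclusion criteria limits each participant's ulcers to "at least 1 cm^2^ up to a maximum of 20 cm^2^ in area" and sets ABI limits, so both measures are known at entry. It adds: "After the participant’s inclusion in the study, regardless of the group allocated, they will be sent to collect laboratory tests". The list that follows includes the cytokine profile. Secondary outcomes (Efficacy) words most continuous outcomes as improvement or reduction: perfusion, quality of life, pain and ulcer area.

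**The concern.** An outcome that passes the normality check gets a t-test under one rule and Mann-Whitney under the other, and nothing says which governs. The first rule also lets the trial data choose the test.

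Neither rule names a baseline covariate or a change score. Eligible ulcers can differ 20-fold in area (20 / 1), so much of the spread at follow-up may already be present at entry. With 20 participants per arm, leaving that spread in the error term widens intervals and lowers power, and chance imbalance at baseline goes uncorrected. At stake is the precision of the continuous secondary outcomes, and whether each has one identifiable planned analysis.

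**Working it through.** **1. The plan's own figure.** Sample size assumes healing of 75% against 30%, 80% power and two-sided 5%. With pooled variance and mean proportion 0.525:

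n = [1.96·√(2·0.525·0.475) + 0.8416·√(0.75·0.25 + 0.30·0.70)]² / 0.45² = (1.384 + 0.531)² / 0.2025 = 18.1, so 19 per arm.

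The stated 20 is reproduced, with about 84% power at 20. This calculation is for a binary outcome, so the point below does not touch it.

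**2. How often the two rules differ.** For independent groups, Wilcoxon rank-sum and Mann-Whitney are the same test, so the rules differ only when normality is not rejected. In simulated trials (20 per arm; 4,000 to 10,000 per scenario):

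- Normal data, 0.8 SD effect: power about 70% for the first rule and 67% for the second. Conclusions at 5% differed in about 6% of trials.
- Normal data, no effect: each rule rejected in about 5% of trials. Conclusions differed in about 1.7%.
- Log-normal data: the rules practically never differed.

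The chance that at least one rule rejects under no effect is (first + second + disagreement) / 2. At correlation 0.5 this is (5.1% + 4.7% + 1.6%) / 2 = 5.7%.

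**3. What baseline adjustment gains.** Inputs: n = 20 per arm (Sample size) and two-sided 5%. The effect d = 0.8 SD and the baseline–follow-up correlation r are assumptions. Power is from the noncentral t distribution with 38 df, critical value 2.024 and noncentrality (effective d)·√(20/2). The effective d is:

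- follow-up value, unadjusted: d
- change score: d / √(2(1 − r)), with equal SD at both times
- ANCOVA: d / √(1 − r²)

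| r | Unadjusted | Change score | ANCOVA |
|---|---|---|---|
| 0.3 | 69% | 0.8/1.183 = 0.676 → 55% | 0.8/0.954 = 0.839 → 73% |
| 0.5 | 69% | 0.8/1.000 = 0.800 → 69% | 0.8/0.866 = 0.924 → 81% |
| 0.7 | 69% | 0.8/0.775 = 1.033 → 89% | 0.8/0.714 = 1.120 → 93% |

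In precision, 40 participants with ANCOVA match 40/(1 − r²) unadjusted, or about 44, 53 and 78. At d = 0.5, power is 34% unadjusted and 37%, 43% and 58% with ANCOVA. Simulated type I error was about 5% throughout.

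**4. Ulcer area.** Healed ulcers have area zero, so step 3 does not carry over directly. It was simulated with the protocol's 75% and 30% healing and baseline area log-uniform on 1 to 20 cm². Residual area was assumed to be 20–100% of baseline if unhealed.

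| Scenario | Planned rule | Square-root ANCOVA | Rank ANCOVA |
|---|---|---|---|
| Healing unrelated to size | 77% | 73% | 79% |
| Larger ulcers heal less often (assumed) | 64–65% | 68% | 75% |

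Under other assumptions, with 30% healing in controls and 50% or 60% with treatment, the square-root model came out ahead of rank ANCOVA. Where larger ulcers heal less often, the powers were 43% against 38% and 58% against 53%, with Mann-Whitney at 24% and 39%. Where healing was unrelated to size (50% with treatment), they were 42%, 39% and 35%. Rank ANCOVA beat the unadjusted test in every scenario, whereas the square-root model did not.

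**The case against.** - **The analysis may be meant for changes.** The outcomes are worded as improvement or reduction, and ABI and some other perfusion measures have change thresholds. If change scores were intended, the gain from ANCOVA at r = 0.7 is about 4 points (93% against 89%), not 24. This stands as a limit on size. The text does not say that changes are tested, and ANCOVA was ahead at each correlation examined.
- **The rules rarely disagree.** This stands: the contradiction is real but modest in effect. A reader might infer that it leaves a wide choice between p-values. Step 2 does not support that, and the Blinding section has external statisticians receive the results blind.
- **Covariates are commonly left to the analysis plan.** True in general, and silence would be no finding. Here the protocol itself fixes two incompatible unadjusted tests, so an analysis plan would have to overrule at least one. The mention of multivariate analysis does not fill the gap, because Cox regression is not a model for these outcomes.
- **Baseline is shown for only some outcomes.** This stands. The visible text covers ulcer area, ABI, the listed laboratory tests and cytokines. It does not show baseline VAS, SF-36, EQ-5D, liver enzymes or clotting times. The assessment schedule, which may include them, is not available here.

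**Conclusion.** The point holds for the continuous secondary outcomes. The section states two conflicting rules, and both ignore baseline values that are known at entry for at least some of these outcomes. The conflict itself costs little. The larger loss is the missing baseline adjustment: about 4 to 24 points of power at an assumed 0.8 SD and correlations of 0.3 to 0.7, and less at high correlation if change scores were intended. The document gives neither effect size nor correlation, so no single figure can be claimed.

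A reader might infer that the trial as a whole is underpowered for this reason. The document does not support that: the outcomes listed under Primary outcomes (total epithelialization and limb salvage) are binary, and the 40 participants follow from the healing rates. Nor do the step 3 gains apply to ulcer area, where the benefit is smaller and depends on how healing relates to size. This is a worthwhile repair to the analysis text, not a defect that threatens the main result.

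**What to change.** 1. In Sample size and Statistics, delete the Shapiro-Wilk step and both between-group rules for continuous data.
2. For each continuous outcome with a baseline measurement, name one analysis: final-visit value on arm plus the baseline value of the same variable (ANCOVA).
3. For ulcer area, make rank-based ANCOVA the main analysis in preference to a square-root model, because healed ulcers are zero.
4. Keep Mann-Whitney only for outcomes with no baseline value.
5. First reconcile the final visit: the Abstract (Methods) has 90 days of monitoring and the Participant timeline has 120.

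The cost is a wording amendment, with no extra participants. No new measurement is needed for outcomes whose baseline is already taken. Recruitment is planned to run to July 1, 2027, so the change can be made before the final analysis.
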